# Measuring Patient Compliance With Remote Monitoring Following Discharge From Hospital After Major Surgery (DREAMPath): Protocol for a Prospective Observational Study

**DOI:** 10.2196/30638

**Published:** 2022-04-06

**Keywords:** digital health, telemonitoring, remote monitoring, telehealth, surgery, hospital, compliance, patient monitoring, wearable technology, smart devices

## Abstract

**Background:**

The incidence of major surgery is on the rise globally, and more than 20% of patients are readmitted to hospital following discharge from hospital. During their hospital stay, patients are monitored for early detection of clinical deterioration, which includes regularly measuring physiological parameters such as blood pressure, heart rate, respiratory rate, temperature, and pulse oximetry. This monitoring ceases upon hospital discharge, as patients are deemed clinically stable. Monitoring after discharge is relevant to detect adverse events occurring in the home setting and can be made possible through the development of digital technologies and mobile networks. Smartwatches and other technological devices allow patients to self-measure physiological parameters in the home setting, and Bluetooth connectivity can facilitate the automatic collection and transfer of this data to a secure server with minimal input from the patient.

**Objective:**

This paper presents the protocol for the DREAMPath (Domiciliary Recovery After Medicalization Pathway) study, which aims to measure compliance with a multidevice remote monitoring kit after discharge from hospital following major surgery.

**Methods:**

DREAMPath is a single-center, prospective, observational, cohort study, comprising 30 patients undergoing major intracavity surgery. The primary outcome is to assess patient compliance with wearable and interactive smart technology in the first 30 days following discharge from hospital after major surgery. Secondary outcomes will explore the relation between unplanned health care events and physiological data collected in the study, as well as to explore a similar relationship with daily patient-reported outcome measures (Quality of Recovery–15 score). Secondary outcomes will be analyzed using appropriate regression methods. Cardiopulmonary exercise testing data will also be collected to assess correlations with wearable device data.

**Results:**

Recruitment was halted due to COVID-19 restrictions and will progress once research staff are back from redeployment. We expect that the study will be completed in the first quarter of 2022.

**Conclusions:**

Digital health solutions have been recently made possible due to technological advances, but urgency in rollout has been expedited due to COVID-19. The DREAMPath study will inform readers about the feasibility of remote monitoring for a patient group that is at an increased risk of acute deterioration.

**Trial Registration:**

ISRCTN Registry ISRCTN62293620; https://www.isrctn.com/ISRCTN62293620

**International Registered Report Identifier (IRRID):**

DERR1-10.2196/30638

## Introduction

Patients undergoing major abdominal and pelvic surgery have readmission rates of over 20% in the first 90 days after surgery [1-3]. Furthermore, 23% of postoperative deaths occur after hospital discharge, of which over 95% occur during the first 3 weeks following discharge [4]. Previously described risk factors for readmission to hospital include reduced functional capacity, chronic inflammatory lung disease, and previous anticoagulation therapy [5-7]. However, consensus is lacking, and patients are therefore not routinely monitored after discharge as patients are deemed to be medically fit. The availability of noninvasive home monitoring devices offers the opportunity to collect and report individualized physiological data, which can serve as surrogates for performance status in the home setting. Home monitoring can also include a means to collect patient-reported outcome measures (PROMs) using easy-to-use media. Such a framework would supplement the standard care discharge pathway, which consists of providing patient information on red-flag symptoms and interval outpatient appointments.

Home monitoring of patients with chronic conditions has previously been shown to be effective, for example, in the management of hypertension and congestive heart failure. A study of patients with hypertension found that during a 48-week period, 91.0% of participants measured their blood pressure regularly [8]. A randomized controlled trial comparing the titration of medication based on self-monitoring of blood pressure versus in-clinic blood pressure measurement in patients with hypertension reported that self-monitoring leads to significantly lower blood pressure [9]. Patient compliance with intermittent self-monitoring of weight and vital signs is similarly high, and benefits have been reported for interactions following changes in physiological status such as a reduction in hospital readmissions; this was found to reduce hospital length of stay from 9.5 days to 0.8 days per patient per year [10]. These reports support that patients can engage with home monitoring and that it is feasible. Furthermore, these studies suggest that engaging patients in the home setting with their own health can help inform their medical team of their health status, encourage patient empowerment, and lead to better health outcomes.

In addition to physiological measurements, PROMs, such as the Quality of Recovery (QoR) questionnaire, have been validated for measuring health status in the postoperative period [11]. The QoR tool and others are not used in routine clinical practice but have been successfully used in clinical trials as a measure of recovery and to discriminate between intervention and control arms [12]. This questionnaire can be applied across a wide range of operative procedures, and its 3 versions (QoR-40, QoR-15, and QoR-9) have been validated with domains for physical and mental well-being [13]. The QoR-40 has been used to track patients for up to 1 month following surgery. To date, the tool has not been used in the context of identifying postdischarge decline, although it has been reported that a low QoR score is independently associated with the development of postoperative complications [14]. As smart technology can be used to collect the QoR, the potential exists to utilize the tool in the postdischarge setting to monitor patients.

Smart devices are similar to their traditional electronic counterparts, but with the added feature of connecting to other devices or networks via different wireless protocols such as Bluetooth, near-field communication, Wi-Fi, 3G, etc. Smart technology has been applied to various medical devices suitable for home use. For example, pacemaker checks can now be safely performed remotely, reducing additional hospital visits [15]. Additionally, consumer-grade, wrist-worn pedometers and heart-rate monitors are commonplace, and many commercially available sphygmomanometers, pulse oximeters and other smart devices are able to wirelessly sync newly collected readings to smartphones. Smartphones can in turn upload data, which can facilitate remote monitoring. In theory, a smart health device can transmit data in real time, allowing for immediate identification and early intervention if deemed clinically necessary. Potential benefits of remote monitoring would enable quicker triage of deteriorating patients, to select patients for clinical review, and to further stratify patients requiring readmission to the index hospital of surgery.

In this study, we will explore the use of smart technology using devices to collect postdischarge data similar to the National Early Warning Score and PROMs in patients who were discharged from hospital after major intracavity surgery. The overarching aim of the study is to test the feasibility of using smart technology to collect physiological data and PROMs from this group of patients.

## Methods

### Study Design

This is a prospective, single-center, observational study to assess patient compliance with smart technology devices using the Home and Locally Observed (HALO) kit. The study will recruit patients undergoing any major intracavity surgery, which is associated with a readmission rate of >15% within 30 days of surgery or >20% in the first 90 days of surgery.

### Objectives

#### Primary Objective

The primary objective of the study is to assess patient compliance with wearable and interactive smart technology in the 30 days following discharge from hospital after major intracavity surgery.

#### Secondary Objectives

The secondary objectives are (1) to explore the relation between unplanned health care events and physiological measurements and PROMs in the postdischarge setting for patients undergoing major surgery, and (2) to explore the correlation between PROMs (QoR-15) and physiological measures in patients in the postdischarge setting.

### Recruitment and Participation Criteria

DREAMPath will recruit patients attending anesthesia and surgical preassessment clinics. It is important to keep patient withdrawals from the study to a minimum; however, a patient may withdraw from the study at any time without prejudice to his or her subsequent treatment.

#### Inclusion Criteria

The inclusion criteria are as follows:

Must be over 18 years of age;Scheduled to undergo or has recently undergone major intracavity surgery with a readmission rate of >15% within 30 days or >20% within 90 days;Able to provide informed written consent to participate.

#### Exclusion Criteria

The exclusion criteria are as follows:

Deemed unfit for surgery;Unable or unwilling to comply with remote monitoring for any reason;Unable or unwilling to fill in a questionnaire in English.

#### Power Calculation

As this is a feasibility study, we aim to recruit 30 patients during this period. It is anticipated that compliance will be achieved for at least 27 of the 30 patients (90%). If 27 patients are observed to comply, then an exact 1-sided 90% CI suggests that the compliance rate will be at least as high as 82%. The timetable for each patient will be 1 calendar month, and patients will be interviewed at the end of the study to collect readmission event data, as well as feedback regarding ease of use.

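### The exact 1-sided 90% lower confidence limit for 27 of 30 compliers is 79%, not the 82% stated

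*Protocol article*

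**What the plan says.** The Power Calculation section of the protocol article gives a target of 30 patients ("we aim to recruit 30 patients during this period") and explains the number by the study being a feasibility study. It then gives the expected result: "It is anticipated that compliance will be achieved for at least 27 of the 30 patients (90" per cent). Precision is described for exactly that result. The condition is "If 27 patients are observed to comply", and the conclusion is that "an exact 1-sided 90% CI suggests that the compliance rate will be at least as high as 82" per cent. The article gives no other confidence limit, margin or power figure for compliance, which is its primary outcome.

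**The concern.** The sentence names the count, the denominator, the type of interval, its sidedness and its confidence level. With all five fixed there is one standard answer, and a limit only 8 points below a point estimate of 90% looks tight for an exact interval on 30 patients.

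If the figure is wrong, the article overstates what 27 compliers out of 30 would show about the primary outcome. A report that repeated 82% would claim a limit its named method does not support. A report that recalculated correctly would disagree with its own published protocol.

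**Working it through.** **Inputs, all from the Power Calculation section:** n = 30; x = 27 (27/30 = 0.90); exact interval; one-sided; 90% confidence, so the tail area is 0.10. Stated lower limit: 0.82.

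**1. The stated figure under the stated method.** The exact (Clopper-Pearson) lower limit is the value p_L that solves

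P(X ≥ 27 | n = 30, p_L) = 0.10,

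which is the 0.10 quantile of a Beta(x, n − x + 1) = Beta(27, 4) distribution. The result is p_L = 0.7907, or 79.1%.

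Check by summing the binomial terms for 27, 28, 29 and 30 compliers at p = 0.7907: 0.0656 + 0.0266 + 0.0069 + 0.0009 = 0.100, as required. The stated 82% is not reproduced. The difference is 82 − 79.1 = 2.9 percentage points.

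**2. The confidence that 82% does carry as an exact bound.** At p = 0.82 the same four terms are 0.1115 + 0.0544 + 0.0171 + 0.0026 = 0.186. The tail area is 0.186 instead of 0.10, so the one-sided confidence is 1 − 0.186 = 0.814, about 81%.

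**3. Whether another reading gives 82%.** Lower limits for 27/30:

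| Method | Level | Lower limit |
|---|---|---|
| Exact (Clopper-Pearson) | 1-sided 90% | 79.1% |
| Exact, lower end of a two-sided 90% interval | 1-sided 95% | 76.1% |
| Exact | 1-sided 80% | 82.4% |
| Mid-P | 1-sided 90% | 80.8% |
| Jeffreys | 1-sided 90% | 81.1% |
| Wilson | 1-sided 90% | 80.8% |
| Wald | 1-sided 90% | 83.0% |
| Wald, continuity-corrected | 1-sided 90% | 81.3% |
| Likelihood ratio | 1-sided 90% | 81.6% |
| Arcsine square root | 1-sided 90% | 82.0% |

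The arcsine limit is sin²(arcsin √0.90 − 1.2816/(2√30)) = sin²(1.2490 − 0.1170) = 0.8195. The likelihood-ratio limit solves 2[ℓ(0.90) − ℓ(p)] = 1.2816², where ℓ(p) = 27 ln p + 3 ln(1 − p), and gives 0.8157.

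Three entries round to 82%. Two are large-sample approximations, which contradict the word exact. The third is exact but at one-sided 80%, which contradicts the stated 90%. Reading the interval as two-sided widens the gap.

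**The case against.** The best defence is that 82% may be a correct number with the wrong label. The arcsine and likelihood-ratio limits both round to it at the stated level, and so does an exact limit at a lower level. It would therefore be wrong to say that no recognised method gives 82%. This stands as a possible account of how the figure arose, and the article does not say which account is true. It does not rescue the sentence, because each explanation requires changing either the word exact or the 90%.

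The second defence is that little hangs on the figure. The study is a small, single-center, observational feasibility study, and its Strengths and Limitations section already concedes the small sample. This limits the consequences, and it also rules out some stronger readings:

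- A reader might infer that the sample size rests on this bound and must be revisited. The article gives feasibility as the reason for 30 patients, and the limit follows as an illustration.
- A reader might infer that a limit below 80% means a criterion is missed, or that 28 compliers are now needed so that the limit exceeds 82%. The article sets no success or null value at 80% or 82%.
- A reader might infer that the final report will carry the wrong limit. The final interval would be computed from the observed data, and the analysis plan is not shown, so this is a risk and not something the document establishes.

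**Conclusion.** The point holds as an arithmetic error. With 27 of 30 complying, the exact one-sided 90% lower limit is 79.1%, and the stated 82% is 2.9 points too high. The distance from the 90% point estimate to the limit is 90 − 79.1 = 10.9 points, where the article implies 90 − 82 = 8.

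The conclusion rests on reading exact in its standard sense, as the Clopper-Pearson limit, and on taking the level and sidedness as printed. It needs no outside figure. The error affects the only precision statement for the primary outcome. It does not affect the sample size, the definition of compliance or any stated decision rule.

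**What to change.** Replace the sentence in the Power Calculation section with: *If 27 of 30 comply (90%), the exact (Clopper-Pearson) 1-sided 90% lower confidence limit is 79%.* Use the same exact method for the interval in the report, so that the two documents agree.

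If a different method or confidence level was in fact used to obtain 82%, the text would have to name it in place of an exact 90% limit.

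The cost is one sentence and a stated limit about 3 points less favourable. No patients are added and nothing else in the design changes.

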### Study Period

Patients will provide consent either prior to having surgery or in the immediate postoperative period while they are still in hospital. At the time of consent, patients will be familiarized with the smart devices and mobile app described. If the patients undergo cardiopulmonary exercise testing (CPET) as part of their routine assessment, the results for this will be recorded. This data will be used to compare the performance of CPET data and smart device data in predicting postoperative complications.

The 4-week monitoring period will commence upon discharge from hospital. Patients will be expected to wear the wearable device at all times, engage with other devices (see the *Remote Monitoring Equipment* section below for the list of devices) twice a day, and fill out 1 daily questionnaire. Compliance will be defined as completion of 70% of the daily PROM questionnaires or wearing the wrist-worn trackers for at least 10 hours per day over the study duration. A minimum of 1 reading in each hour of either step count or heart rate will constitute a successful hour of data collection. Patients will be given the opportunity to contact dedicated personnel in the study team for troubleshooting purposes only. Furthermore, the app provides clear feedback to patients to signal the successful collection of study data. We hope that this measure will help patients feel supported to engage with the study and reduce patient withdrawal. If patients are admitted to the hospital during the monitoring period, they will not be expected to bring the HALO kit to the hospital, and the admission period and subsequent use will not factor into their compliance rate.

The end of the study will be defined as completion of a 30-day follow-up after discharge from the hospital. Patients will be seen at the clinic or contacted by phone to conclude their participation. Postdischarge events will be collected at this time, which is defined as any unscheduled contact with a health care professional, which includes, but is not limited to, general practitioner (GP) visits, accident and emergency (A&E) visits, home visits by primary care team, etc.

All study assessments are summarized in Table 1, and the study flowchart is illustrated in Figure 1. As DREAMPath is an observational study, patients will be able to participate in other trials.

**Table 1 table1:** Assessments for patients who consent to participate in the DREAMPath (Domiciliary Recovery After Medicalization Pathway) study.

Visit	Baseline	Postop	First 30 days after discharge	Appointment after 30 days
Identification and enrollment	✓			
Medical history	✓			
Consent and enrollment	✓			
CPET^a^ (optional substudy)^b^	✓			
HALO^c^ data collection (baseline)	✓			
POMS^d^ score (day 5, postoperatively)^b^		✓		
Blood pressure, pulse oximetry, and temperature (twice daily)			✓	✓
Continuous wrist-worn tracker			✓	✓
QoR-15^e^ questionnaire (once daily)	✓		✓	✓
CD^f^ classification at 1-month postop				✓
Adverse events log and patient preferences				✓

^a^CPET: cardiopulmonary exercise testing.

^b^Optional components depending on clinical pathway.

^c^HALO: Home and Locally Observed.

^d^POMS: postoperative morbidity score.

^e^QoR-15: Quality of Recovery–15.

^f^CD: Clavien-Dindo.

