### Remote Monitoring Equipment

The HALO kit is designed to be used with a cellular broadband device, such as a 4G-capable mobile phone, which can be used to complete questionnaires electronically. The broadband device remotely uploads data to an anonymized database. Patients will be issued a HALO kit before discharge from hospital and will be monitored remotely for 30 days. The HALO kit consists of 4 devices: a wrist-worn device with step count and heart rate measurement capability, an iHealth Air pulse oximeter, an iHealth Track blood pressure monitor, and a Koogeek Thermometer. These devices are shown in Figure 2. Patients without a smartphone will be provided with one for the duration of the study. Patients will be instructed to wear the tracker continuously and will be shown how to measure blood pressure, pulse oximetry, and temperature twice daily (morning and evening). All readings will be transmitted from the respective device to the iPhone wirelessly, with the option for patients to self-enter data if they prefer to. Additionally, they will be asked to complete a QoR-15 questionnaire once daily.

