## Discussion

### Benefits of the Study

The main objective of this study is to measure patient compliance with remote monitoring devices using a multidevice kit for patients in the community setting. This is an important step in order to measure patient engagement prior to any large-scale testing of clinical validity of a remote early warning system in a cohort of patients recovering after major surgery. Similar studies have been reported from prior to the smartphone era [16] and have relied on telemetry to collect data with patients actively reporting data. In the study by Kleinpell et al [16], 725 alarms were generated during a 3-month monitoring period of 10 patients, but only 6 of these alarms led to a clinician consult after phone triage. For remote monitoring to be adopted into routine care, false-negatives need to be kept to a minimum but must still capture all major clinical events. During our data analysis of secondary endpoints, we will explore different early warning systems such as modified versions of the national early warning system [17,18] as well as machine-learning–driven algorithms. Due to the large amount of data being produced, a processing pipeline will be required to ensure that clinical resources are not overburdened by the implementation of remote monitoring.

The current study is designed to be an observational study. Data collected in the study will not be accessible to clinicians until after the completion of the monitoring period, as the study ethics do not allow for clinicians to use this data for clinical decision-making. According to the Medicines and Healthcare Products Regulatory Agency (MHRA) guidelines, any remote monitoring medical apps used that influence clinical decision-making are subject to approval [19]. Similar policies exist in other places including the United States, Australia, and the European Union [20]. If our secondary objective analysis shows that it is feasible to use remote monitoring to pre-empt clinical events, an important next step will be to comply with MHRA and other guidance to ensure that this model is validated for use to facilitate clinical adoption. With a marketplace full of mobile apps that can improve health, regulation is extremely important to ensure that end users are not given false assurances about their health. However, the burden of responsibility must not be passed on to patients to interpret medical data without clinical expertise.

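### The only stated primary result is a count of patients passing an unexplained 70% or 10-hour cut, which does not convey how much monitoring was done; a graded estimate should stand beside it

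*Protocol article*

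**What the plan says.** The Study Period section sets the rule for each patient: "Compliance will be defined as completion of 70% of the daily PROM questionnaires or wearing the wrist-worn trackers for at least 10 hours per day", taken over the study duration. It also defines how wear is scored: "A minimum of 1 reading in each hour of either step count or heart rate will constitute a successful hour of data collection". The Power Calculation section turns this into a count of patients. It says "we aim to recruit 30 patients during this period" and "It is anticipated that compliance will be achieved for at least 27 of the 30 patients (90" percent), and the only precision statement is that "an exact 1-sided 90% CI suggests that the compliance rate will be at least as high as 82" percent.

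The Discussion (Benefits of the Study) gives the purpose: "The main objective of this study is to measure patient compliance with remote monitoring devices using a multidevice kit". It presents this as a step before larger testing of an early warning system. Table 1 and the Remote Monitoring Equipment section schedule a questionnaire every day and continuous tracker wear, and the Data Collection System section describes transfer of the data to a server. The graded record therefore exists for each patient.

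The article gives no rationale for 70% or for 10 hours, and names no graded compliance summary.

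**The concern.** Compliance is recorded on a fine scale, as a share of questionnaires and as hours of wear, but the stated primary result keeps only which side of a cut each patient falls on. On the questionnaire limb with 30 due days, 21 completed forms score the same as 30, and nine consecutive missed days still pass. A result of 27 out of 30 could come from patients who only just reached the cut or from patients who used the kit almost fully. The team planning the next study needs to know which, because the amount of data that arrives determines what an early warning system could use.

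The cuts are also unexplained, so a reader cannot tell whether 70% or 10 hours marks a meaningful level of use.

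**Working it through.** **1. The plan's own figure.** Inputs from the Power Calculation section: n = 30, 27 compliant, exact one-sided 90% limit. The exact (Clopper-Pearson) lower limit is the p that solves P(X ≥ 27 | n = 30, p) = 0.10, which is the 10th percentile of a Beta(27, 4) distribution.

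- Result: p = 0.791. The limit is 79.1%, and the margin is 90.0 − 79.1 = 10.9 points.
- At the stated 82%, P(X ≥ 27 | 30, 0.82) = 0.186, not 0.10. An exact limit near 82% (82.4%) needs only 80% one-sided confidence.

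**2. Margin for a graded mean.** With the patient as the unit, the one-sided 90% margin is t(0.90; 29) × SD / √30 = 1.311 × SD / 5.477. The SD is an assumption because the article gives none.

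| Assumed between-patient SD of % completed | Margin |
|---|---|
| 11 points | 2.6 points |
| 17 points | 4.1 points |
| 20 points | 4.8 points |
| 28 points | 6.7 points |

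SDs of about 11 to 17 points arise if each patient's completion follows a single beta distribution, set so that 90% of patients reach 21 of 30 forms (precision parameter 20 down to 2; the lower end is 10.6 points, margin 2.5). SDs of about 20 to 28 points arise if most patients are engaged and a small group hardly uses the kit. The article does not say which pattern to expect. Both calculations cover the questionnaire limb only, whereas the plan's 90% refers to either limb being met.

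**3. How far the two margins can be compared.** The responder margin of 10.9 points is for the share of patients above the cut; the others are for the mean percentage completed. The interval method also contributes. A simple normal (Wald) limit for 27/30 is 0.90 − 1.282 × √(0.90 × 0.10 / 30) = 0.830, a margin of 7.0 points. In the extreme of 27 full users and 3 non-users, the SD is √(0.90 × 0.10) = 30 points and the margin for the mean is 1.311 × 30 / 5.477 = 7.2 points. There the mean and the proportion coincide, and the graded measure adds no information.

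**4. Information lost on the plan's own target.** Suppose the underlying measure is normal and the target stays the share above the cut, with p = 0.90, z = 1.282 and density φ = 0.1755. The efficiency of the count relative to a normal-model estimate is φ²(1 + z²/2) / [p(1 − p)] = 0.0561 / 0.09 = 0.62, a loss of about 38%. If the target is instead a shift in the mean, the efficiency is φ² / 0.09 = 0.34, a loss of about 66%.

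**The case against.** The strongest reply is that a responder proportion is a legitimate feasibility endpoint. It answers a question that a mean cannot: a mean of 90% does not separate 30 fairly good users from 27 perfect users and 3 non-users. Descriptive summaries of use are commonly left to a full protocol or analysis plan, and the article does not rule them out. All of this stands, and it is why the proportion should be kept.

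Four stronger readings are tempting, and the article does not support them.

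- **A reader might infer that the cut throws away most of the study's precision.** That holds only if the mean replaces the proportion as the target. For the plan's own target the loss is about 38% under a normal model.
- **A reader might infer that the study cannot show how much monitoring was done.** The graded data are collected and kept; it is the stated headline that does not convey it.
- **A reader might set up a test of 90% against 80% compliance and infer a large, general power gain.** The 80% is not in the article, which has no null, no decision rule and no power claim. Under the single-beta model at a one-sided 10% level, the mean has about 78% to 87% power against 41% for the exact count. Part of that gap is discreteness: matched for size, the count has 58%. With engaged users plus low users, the mean has only about 52% to 58%. The gain depends on the assumed model.
- **A reader might infer that 20 completed questionnaires always score the same as none.** Either patient can comply through the tracker. The article also says both "The 4-week monitoring period will commence upon discharge from hospital" and "will be monitored remotely for 30 days"; 70% of 28 is 19.6, so 20 forms pass on one reading, while 70% of 30 is 21.

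**Conclusion.** The point holds as one about what the primary result conveys. The only stated primary result and precision basis is a yes/no at two unexplained cuts, in a study whose purpose is to measure compliance and which already records it in finer detail.

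A graded mean would have a one-sided 90% margin of about 2.5 to 4 points at SDs of 11 to 17 points, or about 5 to 7 points at SDs of 20 to 28. The exact responder limit lies about 11 points below its estimate. The two are different quantities, and the gain rests on an SD and a shape of use that the article does not give; it disappears if patients either use the kit fully or not at all. The main benefit is therefore a more informative result, with better precision likely but not assured. The one firm numerical error is the 82%, which should read 79.1%. None of this makes the planned count invalid.

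**What to change.** In the Study Period and Power Calculation sections, add a graded primary estimate beside the responder proportion:

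- **Questionnaires:** per-patient percentage completed of those due, averaged over patients.
- **Tracker:** per-patient mean number of successful hours per day, averaged over patients. Stating it in hours avoids having to define the hours due.
- **Analysis:** treat each limb separately, with the patient as the unit, and give each mean a one-sided 90% limit (t-based, or bootstrap if the distribution is strongly skewed). Count due days only up to any readmission, as the Study Period section already provides, and reconcile the 4-week and 30-day statements so that the denominator is fixed.
- **Responder proportion:** keep it with its exact interval, correct the limit at 27/30 to 79.1%, and give the reason for 70% and 10 hours, or state that they are conventions chosen by the team.
- **Precision statement:** add the expected margin for the mean over a stated range of SDs.

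Say that the graded means and the proportion are reported side by side as estimates. The plan has no decision rule, so neither needs to govern a test. The cost is a few sentences and a little analysis, with no new patients, visits or measurements. The small downside is more than one headline figure.
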